#### 11.1.2 Disease Parameters

Measurable disease. Measurable lesions are defined as those that can be accurately measured in at least one dimension (longest diameter to be recorded) as  $\geq 20$  mm with conventional techniques (CT, MRI, x-ray) or as  $\geq 10$  mm with spiral CT scan. All tumor measurements must be recorded in millimeters (or decimal fractions of centimeters).

Non-measurable disease. All other lesions (or sites of disease), including small lesions (longest diameter  $< 20$  mm with conventional techniques or  $< 10$  mm using spiral CT scan), are considered non-measurable disease. Bone lesions, leptomeningeal disease, ascites, pleural/pericardial effusions, lymphangitis cutis/pulmonis, inflammatory breast disease, abdominal masses (not followed by CT or MRI), and cystic lesions are all non-measurable.

Target lesions. All measurable lesions up to a maximum of 5 lesions per organ and 10 lesions in total, representative of all involved organs, should be identified as **target lesions** and recorded and measured at baseline. Target lesions should be selected on the basis of their size (lesions with the longest diameter) and their suitability for accurate repeated measurements (either by imaging techniques or clinically). A sum of the longest diameter (LD) for all target lesions will be calculated and reported as the baseline sum LD. The baseline sum LD will be used as reference by which to characterize the objective tumor response.

Non-target lesions. All other lesions (or sites of disease) including any measurable lesions over and above the 10 target lesions should be identified as **non-target lesions** and should also be recorded at baseline. Measurements of these lesions are not required, but the presence or absence of each should be noted throughout follow-up.

#### 11.1.3 Methods for Evaluation of Measurable Disease

All measurements should be taken and recorded in metric notation using a ruler or calipers. All baseline evaluations should be performed as closely as possible to the beginning of treatment and never more than 4 weeks before the beginning of the treatment.

The same method of assessment and the same technique should be used to characterize each identified and reported lesion at baseline and during follow-up.

#### 11.1.4 Response Criteria

#### 11.1.4.1 **Evaluation of Target Lesions**

|                                  |                                                                                                                                                                                           |
|----------------------------------|-------------------------------------------------------------------------------------------------------------------------------------------------------------------------------------------|
| Complete Response (CR):   | Disappearance of all target lesions                                                                                                                                                       |
| Partial Response (PR):    | At least a 30% decrease in the sum of the longest diameter (LD) of target lesions, taking as reference the baseline sum LD                                                                |
| Progressive Disease (PD): | At least a 20% increase in the sum of the LD of target lesions, taking as reference the smallest sum LD recorded since the treatment started or the appearance of one or more new lesions |
| Stable Disease (SD):      | Neither sufficient shrinkage to qualify for PR nor sufficient increase to qualify for PD, taking as reference the smallest sum LD since the treatment started                             |

#### 11.1.4.2 **Evaluation of Non-Target Lesions**

|                                                      |                                                                                                                  |
|------------------------------------------------------|------------------------------------------------------------------------------------------------------------------|
| Complete Response (CR):                       | Disappearance of all non-target lesions and normalization of tumor marker level                                  |
| Incomplete Response/
Stable Disease (SD): | Persistence of one or more non-target lesion(s) and/or maintenance of tumor marker level above the normal limits |
| Progressive Disease (PD):                     | Appearance of one or more new lesions and/or unequivocal progression of existing non-target lesions              |

Although a clear progression of “non-target” lesions only is exceptional, the opinion of the treating physician should prevail in such circumstances, and the progression status should be confirmed at a later time by the review panel (or Principal Investigator).

#### 11.1.4.3 **Evaluation of Best Overall Response**

The best overall response is the best response recorded from the start of the treatment until disease progression/recurrence (taking as reference for progressive disease the smallest measurements recorded since the treatment started). The patient's best response assignment will depend on the achievement of both measurement and confirmation criteria.

| Target Lesions                                                                                                                                                                                                                                                                                                                                  | Non-Target Lesions | New Lesions | Overall Response | Best Response for this Category Also Requires: |
|-------------------------------------------------------------------------------------------------------------------------------------------------------------------------------------------------------------------------------------------------------------------------------------------------------------------------------------------------|--------------------|-------------|------------------|------------------------------------------------|
| CR                                                                                                                                                                                                                                                                                                                                              | CR                 | No          | CR               | ≥4 wks. confirmation                           |
| CR                                                                                                                                                                                                                                                                                                                                              | Non-CR/Non-PD      | No          | PR               | ≥4 wks. confirmation                           |
| PR                                                                                                                                                                                                                                                                                                                                              | Non-PD             | No          | PR               |                                                |
| SD                                                                                                                                                                                                                                                                                                                                              | Non-PD             | No          | SD               | documented at least once ≥4 wks. from baseline |
| PD                                                                                                                                                                                                                                                                                                                                              | Any                | Yes or No   | PD               | no prior SD, PR or CR                          |
| Any                                                                                                                                                                                                                                                                                                                                             | PD*                | Yes or No   | PD               |                                                |
| Any                                                                                                                                                                                                                                                                                                                                             | Any                | Yes         | PD               |                                                |
| * In exceptional circumstances, unequivocal progression in non-target lesions may be accepted as disease progression.                                                                                                                                                                                                                           |                    |             |                  |                                                |
| Note: Patients with a global deterioration of health status requiring discontinuation of treatment without objective evidence of disease progression at that time should be reported as “ symptomatic deterioration ”. Every effort should be made to document the objective progression even after discontinuation of treatment. |                    |             |                  |                                                |

A Clinical Benefit Rate (CBR) consisting of the total number of CR+PR+SD will be used as a secondary endpoint.

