|                                                                                                     | 30                                                                  | 80                                                   | Level -1   |
|                                                                                                     | 40                                                                  | 100                                                  | Level 1    |
|                                                                                                     | 50                                                                  | 120                                                  | Level 2    |
|                                                                                                     | 60                                                                  | 140                                                  | Level 3    |
|                                                                                                     | 70                                                                  | 160                                                  | Level 4    |
|                                                                                                     | 80                                                                  | 180                                                  | Level 5    |
| Erlotinib
150 mg
(only in the
absence of DLT at
dose level 5 of
vinorelbine) | No DLT at dose level
5 of vinorelbine
(80 mg/m  ) | No DLT at dose level
5 of vinorelbine
(180 mg) |            |

Escalation of Erlotinib dose to 150 mg OM will only start if level 5 oral vinorelbine is reached without dose-limiting toxicities with Erlotinib 100 mg OM in each schedule.

The optimal anti-angiogenic dose of oral vinorelbine given in metronomic schedule will be determined from the Circulating Endothelial Cells/Circulating Endothelial Progenitors (CEC/CEP) assays correlations.

Efficacy will be assessed every 2 cycles during maintenance treatment. Each cycle will last 21 days with a window period of 7 days. Patients on the conventional schedule of vinorelbine who respond or have stable disease, vinorelbine will be stopped after 6 cycles and erlotinib continued. Patients on the metronomic schedule of vinorelbine who respond will continue on both vinorelbine and erlotinib.

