## 10. STUDY CALENDAR

Baseline evaluations are to be conducted within 2 weeks prior to start of protocol therapy. Scans and x-rays must be done  $\leq 4$  weeks prior to the start of therapy. In the event that the patient's condition is deteriorating, laboratory evaluations should be repeated within 48 hours prior to initiation of the next cycle of therapy.

|                    | Pre-Study | Wk 1    | Wk 2 | Wk 3 | Wk 4 | Wk 7 | Wk 10 | Wk 13 | Wk 16 | Wk 19 | Wk 22 | >Wk 25         |  | Off Study d |
|--------------------|-----------|---------|------|------|------|------|-------|-------|-------|-------|-------|----------------|--|------------------------|
| Erlotinib          |           | X-----X |      |      |      |      |       |       |       |       |       |                |  |                        |
| Oral Vinorelbine   |           | X-----X |      |      |      |      |       |       |       |       |       |                |  |                        |
| Informed consent   | X         |         |      |      |      |      |       |       |       |       |       |                |  |                        |
| Demographics       | X         |         |      |      |      |      |       |       |       |       |       |                |  |                        |
| Medical history    | X         |         |      |      |      |      |       |       |       |       |       |                |  |                        |
| Concurrent meds    | X         | X-----X |      |      |      |      |       |       |       |       |       |                |  |                        |
| Physical exam      | X         | X       | X    | X    | X    | X    | X     | X     | X     | X     | X     | X e |  | X                      |
| Vital signs        | X         | X       | X    | X    | X    | X    | X     | X     | X     | X     | X     | X e |  | X                      |
| Height             | X         |         |      |      |      |      |       |       |       |       |       |                |  |                        |
| Weight             | X         | X       |      | X    |      | X    |       | X     |       | X     |       | X e |  | X                      |
| Performance status | X         | X       |      | X    |      | X    |       | X     |       | X     |       | X e |  | X                      |

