| Other tests, as appropriate                                                                                                                                                                                                                                                                                                                                                                                                                                           |                 |                                                                                                                                                                                                                                       |   |   |   |   |   |   |   |   |   |                |  |                |
| Pharmacokinetic studies                                                                                                                                                                                                                                                                                                                                                                                                                                               | See section 9.0 |                                                                                                                                                                                                                                       |   |   |   |   |   |   |   |   |   |                |  |                |
| a: vinorelbine and erlotinib: Dose as assigned; oral.
b: Albumin, alkaline phosphatase, total bilirubin, bicarbonate, BUN, chloride, creatinine, glucose, LDH, potassium, total protein, SGOT[AST], SGPT[ALT], sodium.
c: Serum pregnancy test (women of childbearing potential).
d: Off-study evaluation.
e: For subjects who respond or stable at disease , cycle duration will extend from 3 weekly to 6 weekly after 6 months (8cycles) of treatment. |                 |                                                                                                                                                                                                                                       |   |   |   |   |   |   |   |   |   |                |  |                |

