## 11. MEASUREMENT OF EFFECT

Although response is not the primary endpoint of this trial, patients with measurable disease will be assessed by standard criteria. For the purposes of this study, patients should be re-evaluated every 6 weeks for the first 6 months and subsequently every 12 weeks unless disease progression. In addition to a baseline scan, confirmatory scans will also be obtained 6 weeks following initial documentation of an objective response.

For patients who are discontinued from the study for reasons other than disease progression, tumor evaluation by RECIST will not be necessary once new anti-neoplastic cancer therapy has begun.

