#### 11.1.1 Definitions

Evaluable for toxicity. All patients will be evaluable for toxicity from the time of their first treatment with Vinorelbine.

Evaluable for objective response. Only those patients who have measurable

disease present at baseline, have received at least one cycle of therapy, and have had their disease re-evaluated will be considered evaluable for response. These patients will have their response classified according to the definitions stated below. (Note: Patients who exhibit objective disease progression prior to the end of cycle 1 will also be considered evaluable.)

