#### 11.1.5 Duration of Response

Duration of overall response: The duration of overall response is measured from the time measurement criteria are met for CR or PR (whichever is first recorded) until the first date that recurrent or progressive disease is objectively documented (taking as reference for progressive disease the smallest measurements recorded since the treatment started).

The duration of overall CR is measured from the time measurement criteria are first met for CR until the first date that recurrent disease is objectively documented.

Duration of stable disease: Stable disease is measured from the start of the treatment until the criteria for progression are met, taking as reference the smallest measurements recorded since the treatment started.

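### Stable disease can be scored on an off-study scan taken before the first scheduled 6-week assessment, so a patient who leaves early for toxicity can count as a clinical-benefit success

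*Protocol*

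**What the plan says.** All references are to the Protocol.

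- **Qualifying rule for SD.** In the table of Section 11.1.4.3, SD as best overall response must be "documented at least once ≥4 wks. from baseline". The text below that table defines the CBR as the total of CR, PR and SD and sets no minimum duration for SD.
- **Age of the baseline scan.** Section 11.1.3 asks for baseline evaluations close to the start of treatment and "never more than 4 weeks before the beginning of the treatment". The opening of Section 10 sets the same 4-week limit for scans and x-rays.
- **First scheduled re-evaluation.** Section 11 says "patients should be re-evaluated every 6 weeks for the first 6 months".
- **Off-study imaging.** In the Section 10 calendar, the tumour-measurement and radiology rows carry a mark in the off-study column, with the footnote "d: Off-study evaluation". Section 11 waives RECIST evaluation after a discontinuation without progression only once new anticancer treatment has started.
- **Evaluability.** Section 11.1.1 limits response evaluability to patients who have measurable "disease present at baseline, have received at least one cycle of therapy, and have had their disease re-evaluated". Section 5.1 fixes the cycle: "Each cycle will last 21 days with a window period of 7 days".
- **Response population.** The introduction to Section 13 says that every enrolled patient is evaluated for response as well as toxicity, which is wider than Section 11.1.1. Section 13.1 has response, including SD, summarised by dose.

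**The concern.** SD is meant to show that the disease was held for some minimum time on treatment. Here that time is counted from the baseline scan, so days before any drug was taken count towards it. It is also shorter than the interval to the first scheduled scan, so any SD documented before week 6 rests on an unscheduled or off-study scan.

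The patients most likely to have an early off-study scan without progression are those who stop for toxicity. The calendar asks for the scan, and the table then lets it qualify. A patient who could not tolerate the combination can thus enter the CBR as a success, in the same by-dose table that readers will set beside the MTD. With 3 to 6 patients per dose level (Section 13.2), one such classification is visible in the reported rate.

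**Working it through.** The protocol states no figure to reproduce; the check is date arithmetic.

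**Convention and assumption.** Day 0 is the first dose of vinorelbine (the protocol's day 1 of cycle 1). One cycle is taken as 21 days from first dose, without using the 7-day window.

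**Inputs.**
- SD interval: 28 days from baseline (11.1.4.3).
- Baseline scan: day -28 to day 0 (10, 11.1.3).
- At least one 21-day cycle received, and disease re-evaluated (11.1.1, 5.1).
- First scheduled scan: 6 × 7 = day 42 (11).
- Removal after a delay of more than 2 weeks (6).

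**Step 1: earliest scan that can give SD.** Earliest day = max(baseline day + 28, 21).

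| Baseline scan | Baseline + 28 | With the one-cycle rule | First scheduled scan |
|---|---|---|---|
| day -28 | 0 | 21 | 42 |
| day -21 | 7 | 21 | 42 |
| day -14 | 14 | 21 | 42 |
| day -7 | 21 | 21 | 42 |
| day 0 | 28 | 28 | 42 |

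For any baseline scan at least 7 days before first dose, the one-cycle rule sets the floor at day 21. The opening runs from there to day 41.

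**Step 2: split by cause.** If the same 4 weeks ran from first dose, the earliest SD would be day 28 for every permitted baseline date.
- Days 21 to 27 (7 days) come from counting from baseline.
- Days 28 to 41 (14 days) would remain open under a first-dose clock. They come from not tying SD to the 6-week assessment.

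**Step 3: can a toxicity dropout fall in this range?** There are two routes.
- Section 5.4 ends treatment for an unacceptable adverse event with no set day. A patient with a baseline scan on day -14 who completes cycle 1, stops, and has an off-study scan on day 21 has an interval of 14 + 21 = 35 days. That is at least 28, so the patient qualifies.
- Section 6 removes a patient whose delay exceeds 2 weeks. After a full first cycle that is about day 21 + 14 = 35, again before day 42.

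**Step 4: effect on the CBR.** If all patients in the cohort are in the denominator, one patient counts for 1/6 = 16.7 points in a cohort of 6 and 1/3 = 33.3 points in a cohort of 3.

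**The case against.** **The impact is small.** Section 11 says response is not the primary endpoint. The CBR is secondary and described by dose without a test, and escalation and the MTD depend only on DLTs. This stands, and it limits the weight of the point. The 17 and 33 points are also simply what any one reclassified patient is worth in cohorts of that size.

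**The protocol does set a minimum interval, and 4 rather than 6 weeks is a choice.** This stands in part. What is hard to defend is a minimum that includes untreated time and that can be met on treatment only by a scan outside the schedule.

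**Most toxicity removals come later than day 21.** This is fair. Section 5.1 allows continuation at a reduced level if a DLT resolves within 14 days, and Section 6 allows single-agent continuation or a delay of up to 2 weeks. The day-21 case is possible but not the usual one. The delay route, at about day 35, lies in the part of the range that moving the clock alone would not close.

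**Stronger readings that the documents do not support.**
- A reader might infer that, with a 4-week-old baseline scan, SD needs no time on treatment. The one-cycle rule in Section 11.1.1 prevents that. Section 13's looser sentence on all enrolled patients leaves the population unclear, but it sets no separate rule for when SD may be scored.
- A reader might see a contradiction with Section 11.1.5, where "Stable disease is measured from the start of the treatment until the criteria for progression are met". There is none: one rule says when SD qualifies as best response, the other how long it lasted.
- A reader might infer that an older baseline scan always favours SD. Growth between that scan and first dose is part of the measured change and brings a growing tumour closer to the 20% limit for progression, so the effect is not one-sided.
- A reader might infer that the bias grows with dose. That is plausible if toxicity dropouts do, but the protocol gives no dropout rates from which to size it.

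**Conclusion.** The point holds as a minor, upward bias in a descriptive secondary endpoint. Followed as written, the protocol scores SD, and so clinical benefit, on an off-study scan from about day 21 (day 28 with a day-0 baseline scan) up to day 41 that shows neither response nor progression.

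This rests on three assumptions: a cycle counts as 21 days, the one-cycle rule of Section 11.1.1 governs, and the off-study scan is done before any new anticancer therapy. How many patients will be affected cannot be estimated from the document; each would shift the by-dose CBR by 17 points in a cohort of 6 or 33 points in a cohort of 3. The MTD and dose escalation are not touched.

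**What to change.** 1. In the Section 11.1.4.3 table, replace the SD condition with: documented at least once at or after the first scheduled 6-week assessment, counted from first dose, within the visit window. Changing only the time origin would leave days 28 to 41 open.
2. State the width and direction of that window for scans. Section 5.1 gives 7 days for the cycle without a direction. If 7 days early were allowed, the earliest qualifying scan would be 42 - 7 = day 35, about when the Section 6 delay route ends.
3. Add that patients whose only post-baseline scan is earlier and shows neither response nor progression are reported as not assessable for SD, kept in the denominator and not counted as clinical benefit. Keeping them in avoids the opposite bias of dropping them.
4. In the same edit, reconcile Section 11.1.1 with the introduction to Section 13, so that the response population, and hence the CBR denominator, is stated once.

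The cost is a table entry, a sentence or two, and one agreed population definition. No extra scans and no change to treatment are needed. The downside is that the reported CBR may be slightly lower.
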